      - Chronic obstructive pulmonary disease.
      - Impaired renal function.
      - Impaired hepatic function.
      - Type 2 diabetes mellitus.
      - Cerebrovascular disease.
      - Pulmonary hypertension.
    - Myocardial function prior to surgery:
      - Left ventricular dysfunction (whether or not due to previous myocardial infarctions), measured according to the ejection fraction (EF) described in the most recent echocardiography/ventriculography and categorized into:
        - Normal EF > 55%.
        - Mildly impaired function 45-55%.
        - Moderately impaired function 30-45%.
        - Severely impaired function <30%.
        - Functional assessment of heart failure (ordinal variable: NYHA (New York Heart Association) functional class I to IV.
    - Existence of previous liver disease: yes/no (dichotomous variable).
    - Drug allergies: yes/no (dichotomous variable).
    - Smoking history: yes/no (dichotomous variable). If “yes”: current number of cigarettes/day (quantitative variable).
    - Postoperative renal failure: yes/no (dichotomous variable).
    - Classification of acute kidney injury according to the AKIN classification: stages 1/2/3 according to serum creatinine and diuresis (categorical variable).
    - Risk stratification: the EuroSCORE logistical I [21] (Annex I) will be used for preoperative surgical risk assessment: categorical variable.
    - Medical treatment and dosage: yes/no (dichotomous variable) and milligrams/day, of:
      - Antihypertensives.
      - Diuretics.
      - Beta-blockers.
      - Calcium channel blockers.
      - Digitalis.
      - Antiplatelet therapy and withdrawal time prior to surgery.
    - Complexity (categorical variable):
      - Non-coronary surgery.
      - Coronary surgery, single procedure.
      - Coronary surgery, two procedures.
      - Coronary surgery, three or more procedures.
      - Surgery on thoracic aorta.
- Intraoperative variables:
  - Anaesthetic variables:
    - Induction and maintenance: active substances (categorical variable).
    - Volume used in anaesthetic induction prior to CPB: ml (continuous variable).
    - Monitoring: Use of pulmonary artery catheter, yes/no (dichotomous variable).
    - Use of vasoactive and inotropic agents: drugs (categorical variable) immediately after coming off the pump and upon arrival in the ICU.
    - CPB or extracorporeal perfusion variables:
      - Blood products:

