        - Haemoglobin in mg/dl and baseline haematocrit measured at the start of CPB (continuous quantitative viable). Use of blood products in priming and/or during the procedure, yes/no (dichotomous variable).
      - Additives:
        - Use of corticotherapy, yes/no (dichotomous variable).
        - Use of insulin, yes/no (dichotomous variable).
      - Times:
        - Surgery time, in minutes (continuous variable).
        - Aortic cross-clamping time in minutes (continuous variable).
        - Support time, in minutes (continuous variable).
        - Haemofiltration time, in minutes (continuous variable).
        - Time from unclamping to patient decannulation, in minutes (continuous variable).
      - Haemofiltration:
        - Duration, in minutes (continuous variable).
        - Total volume (VTot) extracted in the effluent and Replacement volume (VolR) with plasma solution during CPB, in thousands (continuous variable).
        - Water balance during CPB (VTot-VolR), in millimeters (continuous variable).
      - Metabolic and homeostatic control:
        - Blood gas, acidosis yes/no (dichotomous variable).
        - Glucose, in mg/dl (continuous variable).
        - Temperature, in degrees centigrade (continuous variable).
        - Anion gap in mEq/L (in order to diagnose potential lactic acidosis in cases of poorly-defined metabolic acidosis with levels above 12 mEq/L) [22] (continuous variable).
  - Surgical variables:
    - Surgical procedure performed.
      - Valve surgery, yes/no (dichotomous variable).
      - Coronary surgery, yes/no (dichotomous variable).
      - Combined surgery, yes/no (dichotomous variable).
  - Postoperative variables in ICU.
    - Clinical and scale variables:
      - Intubation time, in hours. (continuous variable).
      - Time of stay in ICU, in hours. (continuous variable).
      - Number of hours on inotropic and/or vasoactive support. (continuous variable).
      - Blood loss.
        - Transfusion of blood products, yes/no (dichotomous variable).
        - Postoperative hospital stay, in days (quantitative variable).
        - Hospital mortality, death yes/no (dichotomous variable).

Hematocrit in percentage (continuous variable).

SOFA score [23] (Annex II) (categorical variable).

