**5.7.- Statistical analysis [24]:**

- Descriptive analysis of variables: measures of central tendency and dispersion will be shown in the case of quantitative variables, while frequencies and proportions will be shown in the case of categorical variables.
- The normality of the variables will be checked using graphs and the Kolmogorov-Smirnov test.
- Homogeneity and comparability between the groups of the two arms of the study in the main confounding factors considered will be verified at the beginning of the study by means of a comparison of proportions (chi-squared test or Fisher's exact test, if necessary) and a comparison of means (Student's t-test and the Mann-Whitney U test in case of non-parametric distributions).
- The intrasubject change over time will be analyzed by comparing paired means using a t-test or Wilcoxon signed rank test (non-parametric variables), quantifying the change in each measure in relation to the baseline reference measure (first sample).
- The bivariate analysis between the CG and PG will be performed using the chi-squared test or Fisher's exact test, if necessary, and using a comparison of means (Student's t-test and Mann-Whitney U test in case of non-parametric distributions).
- In the event of non-homogeneity in any variable between the groups studied, a multivariate analysis will be performed using linear regression.

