**Annex II**

**SOFA Scale**

The SOFA (Sequential Organ Failure Assessment) system was created in a consensus meeting of the European Society of Intensive Care Medicine in 1994 and revised again in 1996. The SOFA system consists of the daily measurement of multiple organ failure based on the scores for six organ systems. Each organ is classified from 0 (normal) to 4 (the most abnormal), providing a daily score of 0 to 24 points. The goal in developing the SOFA was to create a simple, reliable, continuous score that could easily be obtained at each institution.

SOFA score during the first days of admission to the ICU is a good indicator of prognosis. Both the mean and highest score are particularly useful outcome predictors. Regardless of the initial score, an increase in SOFA score during the first 48 hours in the ICU predicts a mortality rate of at least 50%.

| **SOFA score** | **0** | **1** | **2** | **3** | **4** |
| --- | --- | --- | --- | --- | --- |
| **Respirationa**  PaO2/FiO2 (mmHg)  SaO2/FiO2 | >400 | <400  221-201 | <300  142-220 | <200  67-141 | <100  <67 |
| **Coagulation**  Platelets 103/mm3 | >150 | <150 | <100 | <50 | <20 |
| **Liver**  Bilirubin (mg/dl) | <1.2 | 1.2-1.9 | 2.0-5.9 | 6.0-11.9 | >12.0 |
| **Cardiovascularb**  Hypotension | No hypotension | MAP<70 | Dopamine ≤5 or dobutamine (any dose) | Dopamine > 5 or norepinephrine ≤ 0.1 | Dopamine > 15 or norepinephrine > 0.1 |
| **CNS**  Glasgow Coma Scale | 15 | 13-14 | 10-12 | 6-9 | <6 |
| **Kidneys**  Creatinine (mg/dl) or urine output (ml/d) | <1.2 | 1.2-1.9 | 2.0-3.4 | 3.5-4.9 or <500 | >5.0 or <200 |

MAP, mean arterial pressure; CNS, central nervous system; SaO2, peripheral arterial oxygen saturation.

aPaO2/FiO2 ratio should preferably be used. If it is not available, the SaO2 is used

bVasoactive drugs administered for at least 1 hour (dopamine and norepinephrine μg/kg/min)

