**NOC**: This stands for the Nursing Outcomes Classification, which was developed at the University of Iowa. This classification is the result of research carried out at the University of Iowa College of Nursing since 1991, which is still ongoing. It orders and classifies outcomes sensitive to nursing intervention, making it possible to assess the quality of care provided and measure the outcomes achieved in patients who are affected by nursing care.

**Myocardial reperfusion**: A process by which blood is directed back into the myocardial muscle before return of spontaneous circulation.

**SIRS:** Systemic inflammatory response syndrome.

**SvO2**: Venous oxygen saturation

**VO2**: Oxygen consumption

1. EuroSCORE Performing cardiovascular surgery involves a surgical risk for patients, which needs to be assessed. Different mortality prediction systems have been used internationally, but the most widely used in Europe is the model developed in 1995 (EuroSCORE) [18], which was updated in 2011 (EuroSCORE II) [19]. In this country, a validation of EuroSCORE II [20] has been attempted, but given the controversies regarding the use of the model for care purposes, the original system (EuroSCORE) is generally still used. This scale, the logistic EuroSCORE model, acts as a probabilistic model that is useful for determining the risk of hospital morbidity and mortality. [↑](#footnote-ref-2)

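### Section 5.4 labels the 0–24 SOFA score categorical, against Annex II; followed through 5.7, that label points to a comparison that ignores the score's order

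*Protocol*

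**What the plan says.** Protocol 5.4 types each variable. At its end, directly after the postoperative ICU variables, stands "SOFA score [23] (Annex II) (categorical variable"). No bands are given.

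Annex II, to which that entry refers, describes the scale differently: "Each organ is classified from 0 (normal) to 4 (the most abnormal), providing a daily score of 0 to 24 points". It adds: "The goal in developing the SOFA was to create a simple, reliable, continuous score that could easily be obtained at each institution". On how the score is used, it says: "Both the mean and highest score are particularly useful outcome predictors".

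Section 5.7 sets the handling by type. For description, "frequencies and proportions will be shown in the case of categorical variables", and quantitative variables get measures of centre and spread. For the comparison of the two arms it offers a chi-squared or Fisher test, and a comparison of means by t-test or Mann-Whitney. It does not say which variable takes which branch.

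EuroSCORE appears in 5.4 as an adjustment or stratification variable and again among the preoperative variables: "the EuroSCORE logistical I [21] (Annex I) will be used for preoperative surgical risk assessment: categorical variable". The EuroSCORE footnote says that the logistic model "acts as a probabilistic model that is useful for determining the risk of hospital morbidity and mortality". No risk bands are given here either.

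**The concern.** The label in 5.4 and the definition in Annex II cannot both guide the analysis. A 0–24 severity sum whose mean is informative is not an unordered category. If the label is followed, the SOFA comparison becomes a table of score levels by arm. Such a test does not know that 8 is worse than 5, spreads its sensitivity over many degrees of freedom, and gives no direction or size of difference. In a trial of about 40 patients, a real shift in organ-failure severity would then probably go undetected. Because no bands are defined, an analyst who grouped the score would also have to choose the cut points, possibly after seeing the data.

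The EuroSCORE label is a smaller matter of the same kind: a predicted risk turned into undefined groups loses information as a baseline descriptor and as a covariate.

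**Working it through.** **Reading the labels.** Six organ systems at 0–4 each give a maximum of 6 × 4 = 24, so Annex II describes a numeric sum. Section 5.4 has the word ordinal available and uses it for NYHA class, but not for SOFA. Section 5.7 has only two between-arm branches. The type given in 5.4 is the only guide to the branch, and categorical points to chi-squared/Fisher.

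**Plan's own figure.** There is none to reproduce. Section 5.6 expects about 40 patients, and 5.1 gives eight blocks of five (8 × 5 = 40). No significance level, power, effect or SD is stated for SOFA or any other outcome.

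**Inputs.**
- From the protocol: a total of about 40, and a score range of 0–24.
- Assumed: 20 per arm (no allocation ratio is stated); two-sided 5% level; control mean/SD of 6/2, 6/3 or 8/4; a normal score rounded and cut to 0–24; a true shift of d SD. There were 2,000 simulated trials per setting, so the Monte Carlo standard error is at most √(0.25/2000) = 1.1 points.

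**Reference value.** For a comparison of two means, power ≈ Φ(d√(n/2) − 1.96). With d = 0.8 and n = 20: 0.8 × √10 = 2.530; 2.530 − 1.960 = 0.570; Φ(0.570) = 0.716. The simulated t-test gave 0.68.

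**Why the table test differs.** X² = Σ(O − E)²/E on k − 1 degrees of freedom, where k is the number of score levels observed. Reordering the levels leaves X² unchanged. At mean 6 and SD 2.5, about 11 levels occur. The average level then holds 40/11 = 3.6 patients, and the expected count per cell is about 1.8. Cells this sparse would bring in the Fisher option of 5.7, so an exact version (a permutation of the same statistic) is shown too.

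**Power, as the range over the three assumed distributions:**

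| Shift d | Mann-Whitney | Chi-squared, all levels | Exact version, all levels | Chi-squared, 3–4 bands |
|---|---|---|---|---|
| 0.5 | 30–33% | 3–6% | 9–11% | 18–23% |
| 0.8 | 65–66% | 8–14% | 19–23% | 39–47% |
| 1.0 | 83–85% | 15–27% | 32–39% | 60–67% |
| 1.2 | 94–95% | 30–41% | 50–57% | 78–85% |

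The bands were illustrative: 0–4, 5–7, 8 and over; and 0–3, 4–6, 7–9, 10 and over.

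**Share of Mann-Whitney power lost at d = 0.8, within each distribution:**
- Chi-squared on all levels: from 1 − 0.142/0.660 = 78% to 1 − 0.082/0.653 = 87%.
- Exact version: from 1 − 0.226/0.658 = 66% to 1 − 0.188/0.653 = 71%.
- Bands: from 1 − 0.468/0.653 = 28% to 1 − 0.394/0.658 = 40%.

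**Checks.**
- With no shift, rejection rates were 4.3–4.4% (Mann-Whitney), 1.3–2.3% (chi-squared, all levels) and 4.8–5.4% (exact version). Part of the chi-squared loss is therefore conservatism from sparse cells.
- A 16/24 split (two and three patients per block of five), at 6/3 and d = 0.9, gave 74%, 20%, 31% and 53–58% in the order of the table columns.
- Separate runs at SD 2.5 with a 2-point shift (2/2.5 = 0.8 SD) gave 65–66% for Mann-Whitney, 12–13% for chi-squared on all levels, 22% for the exact version and 42% for quartile bands.

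**The case against.** The strongest reply is that 5.7 never sends SOFA to a chi-squared test. It names no test for SOFA, and mapping variables to tests is commonly left to a SAP, which may exist. Section 5.4 also uses its type words loosely: the AKIN stages 1 to 3, plainly ordered, are called categorical as well. This stands in part. The route to chi-squared is an inference from the label, not a stated instruction. The conflict between 5.4 and the annex it cites remains whatever a SAP may say.

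Second, a reader might infer that most of the power is lost in any case. The documents do not support that. It holds for shifts of 0.5 to 1.0 SD if every score level is kept as an unordered cell, which is the literal reading because no bands are given. With three or four bands the loss over those shifts is about one fifth to under one half.

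Third, a reader might take SOFA to be the measure on which the morbidity hypothesis stands. It is not among the dependent variables in 5.4, nor in the list of clinical benefits at the end of Section 3. AKIN stage, intubation hours and hours of inotropic or vasoactive support are also recorded. The lactate comparison is untouched.

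Fourth, it is tempting to count EuroSCORE in the same power loss. It is a baseline and adjustment variable, so its label costs nothing in the organ-failure comparison. Under 5.7, regression is planned only if the arms prove unbalanced, and grouping a risk score for stratification is legitimate if the groups are defined. That Annex I prints only the additive points is no defect, since it explains that the logistic form needs a computer application.

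Finally, relabelling does not make the comparison well powered. At SD 2.5 and a 1.5-point shift, Mann-Whitney has 41% and the t-test 44%. That is true, but it is no reason to discard the ordering.

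**Conclusion.** The point holds as an internal contradiction with a moderate, avoidable cost. Section 5.4 types SOFA against Annex II, and the stated type leads by inference to an analysis that ignores order. At a 0.8 SD shift with 20 per arm, power drops from about 65% to 8–14% (chi-squared) or 19–23% (exact version) with every level kept, and to 39–47% with three or four bands. These figures rest on assumed SOFA means, SDs, shifts and equal arms, none of which the protocol gives. The ranking of the methods was the same in every shifted setting tried; the exact percentages should not be read as properties of this trial.

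The reach is limited to one secondary postoperative ICU variable. The EuroSCORE label is a separate, lesser inconsistency, whose cost lies in the baseline comparison and in any regression adjustment and was not quantified.

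**What to change.** In 5.4:
- Relabel SOFA as an ordinal or quantitative score from 0 to 24.
- State which daily value is compared between arms, for example the highest or the mean, both of which Annex II names, and over which ICU days. Without this, the relabelled variable is still not fully defined.
- Relabel the logistic EuroSCORE as a continuous predicted risk. Use it as a number in the baseline comparison and in any regression under 5.7. If strata are wanted as well, fix their cut points in advance.

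In 5.7, add that SOFA is compared by the Mann-Whitney or t-test already listed, and reported as a difference between arms with a confidence interval.

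The cost is two changed labels and two short sentences. No new data, visits or methods are needed.

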**5.5.- Choice of sample**

**5.5.1.- Inclusion criteria:**

- Patients who sign the informed consent form.
- Patients not undergoing emergency surgery.
- Surgical procedures performed under normothermic conditions.
- Patients with a minimum time of 60 minutes before decannulation (after the end of myocardial reperfusion, unclamping of the aorta and the end of CPB).

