**5.- Methodology**

**5.1.- Study design**

A randomized, patient- and data analyst-blinded clinical trial to compare outcomes in terms of the lactate clearance rates (quantity/unit of time) of the assigned therapy groups. Two treatment groups will be established: one control group without hemofiltration (CG or 1), one group with hemofiltration using a polysulfone filter (PG or 2).

To ensure an unbiased assessment of treatments, randomization will be performed in eight blocks of five patients. The study groups will be equivalent in all aspects except the procedures they undergo.

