**5.5.2.- Exclusion criteria:**

- Patients who do not sign the informed consent form.
- Emergency medical condition in which it is not possible to collect study data.
- Heart condition requiring the use of hypothermia or hyperthermia during CPB.
- Patients without a minimum time of 60 minutes before decannulation (after the end of myocardial reperfusion, unclamping of the aorta and the end of CPB).
- Patients who cannot manage their fluid balance on their own through diuresis prior to CPB.
- Patients who are unable to manage excess volume during the surgical procedure by means of spontaneous or forced diuresis with diuretics (positive cumulative balance despite intravenous bolus of diuretics after 75% of the anticipated duration of CPB according to the course of the surgery).

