**5.8.- Limitations of the study and ethical considerations**

The study design does not allow the use of total blinding, and the perfusionist is aware of the therapy and characteristics of the membrane at all times. According to the literature and standard practice in this country, the use of a control group should not pose any ethical dilemma if certain premises are taken into account.

The only condition that the control group must meet is that the patients must be able to manage their fluid balance by themselves, as a fluid overload has been shown to be harmful. This may mean that the patients in the control group have better renal function than those in the other group, or at least better initial diuresis. However, the primary objective is not to measure or evaluate perioperative renal function. In addition, a hemofilter will be available for use if control patients are not able to manage their fluid balance through diuresis. Finally, if surgery times are shorter in the control group, the lactatemia levels may be lower than in the other group with a longer duration. If this is the case, we will stratify the treatment groups by selecting cases with a shorter duration. In any case, a minimum time of 60 minutes is established from start of CPB + CUF and to the end of CPB.

It will be carried out according to the international ethical recommendations (the Declaration of Helsinki and the Oviedo Convention), since the use of the best available therapy according to the patients' circumstances is contemplated at all times.

In order to safeguard confidentiality, all personal data collected as part of this study will be treated in accordance with Organic Law 15/1999, of December 13, on personal data protection.

Likewise, informed consent will be requested for surgery that includes the usual CPB procedures with or without hemofiltration.

Informed consent will also be requested for use of any data deriving from medical records and analytical determinations. Access to personal information will be restricted to the investigator and authorized personnel and all of them will be obliged to maintain confidentiality. If the work is published, the patients' identity will remain anonymous at all times.

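### The 60-minute minimum for eligibility is defined by two intervals that do not agree, and as written it can remove patients after allocation

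*Protocol*

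**What the plan says.** Section 5.5.1 admits patients with a "minimum time of 60 minutes before decannulation (after the end of myocardial reperfusion, unclamping of the aorta and the end of CPB". Section 5.5.2 mirrors this by excluding "Patients without a minimum time of 60 minutes before decannulation", followed by the same parenthesis.

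Section 5.8 first discusses what to do if control operations are shorter, then adds that, whatever happens, "a minimum time of 60 minutes is established from start of CPB + CUF and to the end of CPB".

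Section 5.1 defines the comparator as "one control group without hemofiltration (CG or 1". Section 5.8 provides a fallback: "a hemofilter will be available for use if control patients are not able to manage their fluid balance through diuresis".

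Section 5.4 lists three separate durations: "Time from unclamping to patient decannulation, in minutes (continuous variable", "Support time, in minutes (continuous variable" and "Haemofiltration time, in minutes (continuous variable". The protocol itself thus treats these as different quantities. It does not state when randomization takes place relative to CPB, and it does not say whether the 60 minutes are anticipated or achieved.

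**The concern.** An eligibility rule should give the same answer whoever applies it. Here two people following the protocol faithfully could include different patients, depending on whether they work from section 5.5 or section 5.8.

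Three features make this more than untidy wording.

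- **The rule selects on duration.** Section 3 says that longer CPB worsens hyperlactatemia in patients in whom it is hard to control. Section 5.8 says that shorter control operations could lower control lactate. Duration is therefore tied to the main outcome.
- **The achieved duration is learned late.** It is known only during or after CPB. The allocated treatment is continuous filtration during CPB, so by then it has started. Applied as achieved time, the criterion removes patients who have already been allocated and treated.
- **The perfusionist knows the arm.** Section 5.8 says so. An ambiguous rule, applied late by or around someone who knows the allocation, leaves room for selection that differs between groups.

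**Working it through.** **Step 1. The two rules side by side.**

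| | Sections 5.5.1 and 5.5.2 | Section 5.8 |
|---|---|---|
| Start | Literal reading: end of reperfusion, unclamping, or end of CPB (three events named) | Start of CPB + CUF |
| End | Decannulation | End of CPB |
| Length | 60 min | 60 min |

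If the section 5.5 interval starts at the end of CPB, the two intervals do not overlap at all.

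**Step 2. Do they classify patients differently?** The protocol gives no times, so the timelines below are assumed and serve only to test the logic. Times are minutes from CPB start.

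| Patient | Unclamp / end CPB / decannulation | End CPB to decannulation | Unclamp to decannulation | CPB start to end |
|---|---|---|---|---|
| A | 70 / 90 / 105 | 105 − 90 = 15, fails | 105 − 70 = 35, fails | 90, passes |
| C | 25 / 50 / 115 | 115 − 50 = 65, passes | 115 − 25 = 90, passes | 50, fails |
| D | 30 / 75 / 92 | 92 − 75 = 17, fails | 92 − 30 = 62, passes | 75, passes |

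A and C show disagreement in both directions. D shows that section 5.5 is ambiguous within itself, because the answer depends on which named event starts the count.

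**Step 3. The charitable reading.** Suppose the parenthesis only describes when decannulation happens. Section 5.5 then has an end but no start. Borrow the start of CPB from section 5.8. A patient with 50 minutes of CPB who is decannulated at 65 minutes passes section 5.5 (65 ≥ 60) and fails section 5.8 (50 < 60). Since decannulation follows the end of CPB, disagreement on this reading runs one way only. It is limited to patients with under 60 minutes of CPB who are decannulated at 60 minutes or later.

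**Step 4. The CUF component.** Start and end of CPB can be timed in every patient. A CUF start is planned only in the filtration group and occurs in a control only through the fallback hemofilter. If CPB + CUF means CPB, with filtration where assigned, the interval is the same in both arms. If it means the time when both are running, it is not. As an assumed example, with 70 minutes of CPB and a filter started at minute 15, a filtration patient has 70 − 15 = 55 minutes and fails. A control timed on CPB alone has 70 and passes.

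**Step 5. Size.** The planned number reproduces as 8 blocks × 5 patients = 40 (sections 5.1 and 5.6). No alpha, power, effect or SD is given. To show only how sensitive so small a trial is, assume 20 per arm, two-sided alpha 0.05, 80% power and losses equal across arms. The detectable standardized difference is (1.960 + 0.842) × √(2/n per arm).

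| Assumed loss | Patients left | Detectable difference (SD) | Power for 0.886 SD |
|---|---|---|---|
| 0% | 40 | 0.89 | 80% |
| 10% | 36 | 0.93 | 76% |
| 25% | 30 | 1.02 | 68% |
| 50% | 20 | 1.25 | 51% |

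The loss percentages are not estimates. The table covers precision only; selection that differs by arm would add bias that it does not show.

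**The case against.** The best defence is that there is one rule, stated incompletely. The parenthesis names three events, which cannot jointly be one starting point, so it may merely describe when decannulation occurs. Section 5.8 then supplies the missing start. The operative criteria in 5.5.1 and 5.5.2 agree with each other, and the discordant sentence sits in a limitations section. The durations in section 5.4 would allow the unclamping-to-decannulation interval, and CPB time if that is what support time means, to be checked afterwards.

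Much of this is fair. It narrows the conflict, but step 3 shows that it does not remove it: the end events still differ and nothing sets precedence. Recording the durations helps reporting but does not settle who is eligible.

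Three stronger readings are tempting and not supported.

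- A reader might infer that the section 5.8 interval does not exist in the control arm. Only its CUF component lacks a planned start there. No sentence says that the rule will be applied differently by arm; the wording merely permits it.
- A reader might infer that the two rules are mutually exclusive. They conflict as definitions of one criterion, but a patient can satisfy both. How far the start events differ depends on how the parenthesis is read.
- A reader might put typical operating times into the two rules and infer that one of them nearly empties the trial. The protocol gives no times, so any such count reflects the assumptions alone. A reading that left almost nobody eligible would also sit badly with the cohort of about 40 expected in section 5.6.

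**Conclusion.** The point stands as an inconsistency in an eligibility rule. The end events differ on every reading, the start events differ on the literal one, and no sentence decides between them. The CUF component adds a risk, not a certainty, that the rule works differently by arm. Whichever interval is meant, applying it as achieved time can remove allocated patients on a duration linked to lactate, with the perfusionist aware of the arm.

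Two assumptions carry the last part: that allocation precedes the point at which the time is known, which filtration throughout CPB requires, and that the criterion is judged on achieved time, which the protocol neither states nor rules out. The number of patients affected is unknown. Eligibility is fixed in the protocol, so this is not a detail that an analysis plan would be expected to settle.

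**What to change.** Reconcile sections 5.5.1, 5.5.2 and 5.8 into one interval, with one start event and one end event that can be observed identically in both arms. Which interval is meant is for the investigators to say. CPB start to CPB end is one candidate and is already collected if that is what support time in section 5.4 means; the term should then be defined.

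State that the criterion is judged as anticipated time before allocation. Section 5.5.2 already uses an anticipated CPB duration for another criterion, so the idea is not foreign to the protocol. State also that allocated patients whose time turns out shorter stay in the main comparison.

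The amendment touches three sections and needs no new data. It does more than tidy wording, because it settles when the criterion is judged and who is analysed. The downside is that a few short-CPB patients with fewer lactate samples remain in the analysis.
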